### Microbiome and metabolomic analyses

4.4

Pre-specified mechanistic hypothesis: The TCM intervention modifies gut microbial community structure and host metabolic profiles in patients with advanced NSCLC, remodels the immune microenvironment via the gut-lung axis, and synergistically enhances anti-tumor therapeutic effects.

Sample collection and handling SOP: Fecal samples are collected at baseline and after two treatment cycles. Fresh fecal samples are immediately stored at −80 °C and shipped to the third-party laboratory on dry ice. Repeated freeze-thaw cycles are prohibited. Timestamps for sample collection, storage and transportation are fully documented.

Quality control (QC): For microbiome assays, DNA concentration and integrity are used for sample qualification; samples with severe DNA degradation or insufficient concentration are excluded. Negative and positive controls are included for sequencing. For metabolomics, pooled QC samples are interspersed among study samples to monitor instrument stability; ion features with excessive signal variation are filtered out. All QC thresholds are predefined and implemented by the contracted laboratory.

Statistical workflows: Alpha- and beta-diversity and differential taxa analyses are performed for microbiome data. Differential metabolite screening is conducted for metabolomics data. The Benjamini-Hochberg procedure is applied for FDR correction to control false-positive rates. Correlation analyses are performed to explore associations among microbes, metabolites and clinical endpoints. Analytical scripts are pre-defined; post-hoc modification by the testing vendor is not permitted. Raw datasets and QC reports are fully archived.

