**Discussion:**

We predict that by repairing the intestinal barrier and adjusting the stability of intestinal flora to enhance the efficacy of immunotherapy for non-small cell lung cancer, non-small cell lung cancer patients will improve spleen deficiency and quality of life through JPGC. This study used TCM syndrome analysis, laboratory tests, imaging examinations and other indicators to evaluate the clinical efficacy and safety of JPGC. Fecal metabolomic analyses will be implemented in trial subjects to explore the latent synergistic mechanisms associated with JPGC intervention. This is a traditional Chinese medicine trial to observe and treat advanced NSCLC characterized by spleen deficiency syndrome by directly regulating intestinal flora. If successful, this discovery will have value in antitumor therapies and drug development, especially in the “immune era.”

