### Intervention method

3.8

Treatment group: Jianpi Guchang granules, 1 bag each time, twice a day. Combined with immunotherapy (a. Define and stratify according to PD-L1 tumor proportion score and EGFR/ALK/KRAS/BRAF status, driver gene negative, any PD-L1 level: platinum-containing chemotherapy combined with immunotherapy is an important first-line option. When PD-L1 TPS>1% subjects, combined PD-1/PD-L1 immunotherapy is allowed. b. Choose a chemotherapy regimen that complies with guideline recommendations). There is a course of treatment every 21 days, and there are a total of 4 courses of treatment.Control group: The control group received oral granules at 1/10 of the original dose of the treatment group, and other treatment options were the same as those in the treatment group. Every 21 days is a course of treatment, and a total of 4 courses of treatment are provided.

Granules:The granules and placebo used in the trial were produced by Shanghai Wanshicheng Pharmaceutical Co., Ltd.

**Table 2** presents the timeline for subject screening, trial interventions and study assessments.

**Table 2 T2:** Trial timeline.

Visit	Screening	Drug intervention period (weeks)				After drug withdrawal	Further follow-up (Every three months until 3 months before the end of the project or the patient's death)
	0d	3	6	9	12	3 months	
Informed consent form	×						
Demographic information	×						
Inclusion and exclusion criteria	×						
General information	×						
Vital signs	×						
History of NSCLC and its treatment	×						
History of other diseases and their treatments	×						
TCM syndrome score	×	×	×	×	×		
ECOG score	×	×	×	×	×		
EORTC QLQ-C30	×	×	×	×	×		
Routine blood tests	×		×		×		
Liver function	×		×		×		
Renal function	×		×		×		
Serum and stool samples collection	×		×		×		
Intestinal barrier function	×		×		×		
Gut flora	×		×		×		
Inflammatory cytokines	×		×		×		
T cell subsets	×		×		×		
Imaging evaluation (RESIST1.1)	×		×		×	×	×
Adverse events		×	×	×	×	×	×
Release drugs/placebo	×	×	×	×			
Retrieve empty packages		×	×	×	×		
Drug combination	×	×	×	×	×	×	×
Survival					×	×	×

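### The metabolomics steps listed in 4.4 do not separate compounds from the granules from host or microbial metabolites, so ingested product can be counted as metabolic change

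*Protocol article*

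**What the plan says.** The mechanistic hypothesis in 4.4 is that "The TCM intervention modifies gut microbial community structure and host metabolic profiles in patients with advanced NSCLC". The abstract names the matrix: "Fecal metabolomic analyses will be implemented in trial subjects to explore the latent synergistic mechanisms associated with JPGC intervention".

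On timing, 4.4 states that "Fecal samples are collected at baseline and after two treatment cycles". Treatment lasts four 21-day courses (3.8), so that sample falls at week 6, during dosing. Table 2 adds a stool sample at week 12, the end of dosing.

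Table 1 lists nine ingredients: eight of plant or fungal origin and one of animal origin. On the comparator, 3.8 says "The control group received oral granules at 1/10 of the original dose of the treatment group", whereas the Methods paragraph of the abstract describes it as a placebo.

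The test itself is described in 4.4 as follows: "Differential metabolite screening is conducted for metabolomics data. The Benjamini-Hochberg procedure is applied for FDR correction to control false-positive rates". The other metabolomics steps named there are pooled QC samples, a rule that "ion features with excessive signal variation are filtered out", and correlation with microbes and clinical endpoints. Section 4.10 adds sensitivity analyses that exclude antibiotic users and adjust for proton pump inhibitors, probiotics and diet. The analysis scripts are said to be pre-defined and closed to later modification by the testing vendor. They are not shown.

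**The concern.** The hypothesis is about what the patient's body and gut flora do. The measurement is of everything in the stool, including whatever the patient swallowed. Unabsorbed constituents of an oral herbal product, and their gut breakdown products, are to be expected there, in amounts that differ by arm. Such a feature differs because of dosing, whether or not anything in the host has changed.

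Two things are at stake. First, the list of differential metabolites can contain exposure markers presented as metabolic effects, and the same features can go on to the correlations with microbes and clinical endpoints. Second, each of these rejections raises the Benjamini-Hochberg cut-off applied to the remaining features, so more null host metabolites pass than a host-only analysis would allow.

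**Working it through.** **1. What each listed step does to a product-derived feature**

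- Pooled QC and the signal-variation filter remove ions measured unstably. A granule compound measured stably passes.
- Benjamini-Hochberg guards against chance findings. A product compound truly differs with exposure, so rejecting it is correct for that feature, but it says nothing about the host.
- The adjustments in 4.10 cover other drugs and diet, not the study product.
- The contrast (between arms or before versus after) is not stated. Between arms is the natural reading in a randomised trial, and a before/after contrast has the same problem.

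**2. Inputs**

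The documents give no figure for the metabolomics screen, so there is none to reproduce. The group size follows from 2.2: (0.25 + 0.09)/0.16 × (1.96 + 1.282)² = 22.3, rounded up to 23, with 28 recruited per arm. After the planned 20% loss, 28 × 0.8 = 22.4 remain. I use 22 to 28 per arm, or 25 as a middle value. The tenfold exposure ratio is from 3.8; a comparator free of product would make the contrast larger.

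Assumed: m = 1000 independent features, K product-derived features (0, 10, 50, 100), no host effect, FDR level q = 0.05, and a between-patient SD of 1.0 to 2.5 on the natural-log scale.

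**3. Would a tenfold difference be detected?**

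The standardised difference is ln(10)/SD = 2.303/SD. Power comes from the noncentral t distribution with 2n − 2 degrees of freedom and noncentrality (2.303/SD) × √(n/2). For one feature at p < 0.001, with 22 to 28 per arm:

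| log-SD | Power |
|---|---|
| 1.0 | about 1.00 |
| 1.5 | 0.93-0.99 |
| 2.0 | 0.61-0.79 |
| 2.5 | 0.33-0.49 |

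Detection is likely at moderate variation and far from certain at high variation.

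**4. Effect on the host features**

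If all K product features are rejected, at least one null host feature is also rejected whenever the smallest host p-value is at or below q(K + 1)/m. The chance of that is 1 − [1 − q(K + 1)/m]^(m − K):

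- K = 0: 1 − (1 − 0.00005)^1000 = 4.9%
- K = 10: 1 − (1 − 0.00055)^990 = 42%
- K = 50: 1 − (1 − 0.00255)^950 = 91%
- K = 100: 1 − (1 − 0.00505)^900 = 99%

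These apply when every product feature is detected. Simulation with between-patient noise on the product features, 25 per arm, gives the range over the assumed SDs:

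| Product features | Chance of at least one false host metabolite |
|---|---|
| 0 | about 5% |
| 10 | 16-44% |
| 50 | 67-92% |
| 100 | 90-99% |

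The low ends belong to high variation, where fewer product features are rejected. The figures carry simulation error of a few percentage points.

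The expected number of false host metabolites is modest. With all K rejected it is about aK/(1 − a), where a = q(m − K)/m. For K = 10, a = 0.0495, giving 0.5; for K = 50, a = 0.0475, giving 2.5; for K = 100, a = 0.045, giving 4.7.

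**5. Overall FDR**

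With product features counted as true differences, the FDR is q(m − K)/m: 4.95%, 4.75% and 4.5% for K = 10, 50 and 100. The procedure keeps its promise for the whole list. Control is lost only within the host subset.

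**The case against.** The strongest reply is that this is a condensed article. A filter or annotation step for product compounds could sit in the pre-defined scripts or the laboratory's procedures. That stands as a limit: a reader might infer that the trial has no such step, and the documents show only that none is described. The point survives because 4.4 does set out its filters and corrections, and those listed do not deliver a statement about the host. If the step exists, one sentence closes the matter.

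A reader might also infer that the product will be reported as host change, or that the plan would confirm its hypothesis whatever happens. Neither is supported. How many granule compounds reach stool, how they are annotated and how they are interpreted are not given. No confirmation criterion is set. The analysis is exploratory, and 5.3 says that the study cannot settle molecular targets or causal pathways.

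Nor is the Benjamini-Hochberg step wrong: it is valid for the family it is applied to, and the absolute number of false host features is small.

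Finally, flagging features merely because they are absent at baseline would be a poor remedy. It can remove metabolites newly induced by treatment, and it can miss product compounds already present from diet or earlier herbal use. I accept this, and the fix reflects it.

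**Conclusion.** The point holds in a limited form: following the steps in 4.4 as written, product-derived compounds can be listed as differential metabolites and read as host change, and no stated step prevents it. They also weaken error control among the host features, from about 5% to 16-44%, 67-92% or 90-99% for 10, 50 or 100 product features. Those figures rest on an assumed feature count, product-feature count, SD range and FDR level, with independent features, and are illustrative. The mismatch between hypothesis and measurement does not depend on them. The primary endpoint and the sample size are unaffected. It is worth correcting before the samples are analysed, because the remedy is cheap and the scripts are meant to be fixed in advance.

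**What to change.** In 4.4 and the pre-defined scripts:

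1. State the contrast and the FDR level.
2. Before differential testing, flag features that match an extract of the JPGC granules or the control granules run in the same batch, or known constituents of the Table 1 ingredients. Use absence from all baseline samples, taken over both arms, as a supporting flag only.
3. For the host claim, run differential testing, Benjamini-Hochberg and the correlations on the unflagged features.
4. Report flagged features separately as exposure markers, in their own Benjamini-Hochberg family.
5. Show the unfiltered result as a sensitivity analysis.

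The descriptions of the comparator in 3.8 and the abstract must be reconciled, since they define the exposure contrast.

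The cost is one script step and a few reference injections. The downside is that some microbially transformed herb compounds of interest move to the separate list. Patient procedures, the sample size and the primary analysis do not change.

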### Safety observations

4.5

General vital signs, laboratory test results (including liver function and renal function tests) will be recorded before enrollment and during each treatment period (visits1,2, 3 and 4). Any possible adverse events (AEs) that occurred during all treatment periods were recorded. If the subject has abnormalities in indicators after treatment and no abnormalities before enrollment, regular monitoring will be performed until the indicators return to normal; all adverse events will be followed up until complete resolution.

### Research implementation and safety monitoring

4.6

Composition of DSMB: 3 independent external experts, including 1 clinical oncology expert, 1 clinical statistics expert, and 1 pharmacology/safety expert; all members have no conflicts of interest with this study and will not participate in enrollment and clinical execution.

2) Interim analysis plan: One interim analysis is preset. The interim analysis will only be performed by independent statisticians, and the DSMB will review the safety and effectiveness data.

3) Toxicity evaluation uses CTCAEv5.0 uniformly, and all AE/SAE are graded and recorded according to this standard.

4) Preset stopping rules: including ① serious unacceptable safety risks; ② interim analysis shows that the benefit of the trial group has indeed reached the preset termination limit; ③ enrollment efficiency is seriously insufficient; the sponsor will decide whether to terminate the trial after the DSMB gives recommendations.

### Trial quality control

4.7

All study personnel (including site investigators and study drug pharmacists) shall complete standardized trial-specific training prior to study initiation. Investigators shall complete case report forms (CRFs) fully in compliance with the study guidelines; CRFs constitute immutable source documents. All laboratory and imaging test results generated during the trial must be documented, with original or duplicate reports appended to the corresponding CRFs. Any laboratory parameters markedly outside clinical reference ranges shall be verified and annotated with explanatory notes by the study physician. Clinical monitors conduct routine on-site monitoring visits to investigative sites, perform random source data verification, host periodic thematic meetings, and deliver prompt feedback through monitoring reports and project synopses to sustain continuous improvement of trial quality.

Investigators will truthfully fill out the case report form, and inspectors will regularly check the data. The original record should be kept clearly visible during modifications, and the corrections should be signed and dated by the researcher. The case report form is reviewed by the supervisor and submitted to the clinical trial data manager. Transfers between researchers, supervisors and data managers will be specially recorded. Prior to data entry, the data manager shall conduct secondary data validation. All queries and corresponding resolutions shall be archived as query forms for retrospective review.

### Data management

4.8

After the completion of the trial, the original data and collected samples shall be retained for a minimum of 5 years. All activities including trial safety monitoring, verification of the accuracy of subject information, protection of subjects’ privacy, and assessments concerning amendments to the study protocol or trial termination shall be directly undertaken by the trial research team.

### Subject follow-up

4.9

The main forms of follow-up are telephone follow-up and outpatient follow-up. Patients are instructed to follow up one week after discharge. If the patient does not go to the outpatient follow-up, telephone follow-up will be changed to once every 3 months, and call records will be made. The survival period is calculated from the day of the first immunotherapy administration to the time of death recorded in the medical record or the patient’s death. The difference between the two times is the survival period; the last follow-up time for surviving patients and patients lost to follow-up is recorded as the censored time, and the survival time is expressed in months. The project conducted the last telephone follow-up visit for all enrolled patients as of the first 3 months.

### Statistical analysis plan

4.10

Data processing was carried out with SPSS26.0 statistical software. The measurement data gives the mean, standard deviation, minimum, maximum, median, etc., which are expressed as mean ± standard deviation; the counting data gives the frequency distribution and corresponding percentages. T-test was used to compare data groups with normal distribution measurement data; rank-sum test was used for non-normal distribution measurement data, chi-square test was used for counting data, qualitative variables and correlation. Log-rank test was used for survival time and survival rate after treatment. Survival analysis was carried out using Kaplan-Meier method. Using α=0.05 as the test criterion, P<0.05 as the difference is statistically significant.

Information on the start and end times and treatment courses of antibiotics, proton pump inhibitors (PPIs), and probiotics during the trial will be collected, and key dietary covariates will be collected; subjects will not be forced to withdraw from the study due to the use of the above drugs. The preset sensitivity analysis included: excluding subjects who used antibiotics during follow-up; incorporating PPI, probiotics and dietary covariates into the model for correction to evaluate the robustness of the primary endpoint and microbiome and metabolome analysis results.

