### Exploratory study endpoints

4.3

Including TCM syndrome integral, EORTC QLQ-C30, ECOG score, intestinal barrier, intestinal flora, inflammatory cytokines, T cell subsets, etc.

TCM syndrome integral: TCM syndrome integral record time refer to evaluation time point in **Table 2**.

TCM Syndrome Points:

The severity of primary symptoms and secondary symptoms was divided into 0, I, II and III according to the single scoring standard of primary symptoms and secondary symptoms. Grade 0: asymptomatic, 0 points; Grade I: mild symptoms, not affecting daily life and work, 1 point; Grade II: moderate symptoms, partially affecting daily life and work, 2 points; Grade III: severe symptoms, affecting daily life, difficult to persist in work, 3 points.

The evaluation of syndrome efficacy includes changes in main symptoms, secondary symptoms, signs, and tongue images. It is calculated using nimodipine method. The efficacy index = [(pre-treatment points subtract post-treatment points)/pre-treatment points]×100%, which is divided into 4 levels: clinical recovery, effective, and ineffective.

1. Clinical recovery: The main symptoms, secondary symptoms, and signs disappeared or basically disappeared, the tongue picture basically returned to normal, and the efficacy index was ≥95%;2. Effective effect: The main symptoms, secondary symptoms, signs, and tongue symptoms have been significantly improved, with 70%≤ efficacy index <95%;3. Effective: The main symptoms, secondary symptoms, signs, and tongue symptoms have improved, 30%≤ efficacy index<70%;4. Ineffectiveness: The main symptoms, secondary symptoms, signs, and tongue manifestations have not been significantly improved or even worsened, and the efficacy index is<30%.

Quality of life QOL score and weight monitoring: application of EORTC QLQ-C30 scale.

A standardized PRO management and compliance monitoring plan is preset for the study: questionnaires are filled out independently at baseline, every 2 treatment cycles, and on site at the end of treatment. The investigators only provide process answer questions and do not induce answers. The questionnaire completion rate, missing item rate and compliance were monitored throughout the process; cases with low compliance were recorded, and the robustness of the results was verified through sensitivity analysis.

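### By the plan's own rule the four ordered TCM efficacy grades would go to a chi-square test that ignores order, and chi-square is the only method named for correlation: a minor mismatch in exploratory analyses

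*Protocol article*

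**What the plan says.** Section 4.10 gives three rules by type of data. For normal measurements: "T-test was used to compare data groups with normal distribution measurement data". For the rest of the measurements: "rank-sum test was used for non-normal distribution measurement data". For categorical data: "chi-square test was used for counting data, qualitative variables and correlation". It names no test for ordered categories and no correlation coefficient.

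Section 4.3 lists the exploratory endpoints: "Including TCM syndrome integral, EORTC QLQ-C30, ECOG score, intestinal barrier, intestinal flora, inflammatory cytokines, T cell subsets, etc". It derives a percentage from the TCM points, "The efficacy index = [(pre-treatment points subtract post-treatment points)/pre-treatment points]×100", and grades it, "which is divided into 4 levels: clinical recovery, effective, and ineffective". That sentence names only three levels, but the numbered list after it gives four, cut at 30%, 70% and 95% of the index.

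Section 4.4, on the microbiome and metabolome, states: "Correlation analyses are performed to explore associations among microbes, metabolites and clinical endpoints". It names no coefficient. It does provide for false discovery rate control and says that the analysis scripts are defined in advance.

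**The concern.** The four grades have a natural order. A Pearson chi-square on the resulting 2×4 table has 3 degrees of freedom and gives the same result however the columns are arranged, so a steady move towards better grades earns no more credit than a scatter of the same size. A rank test puts its single degree of freedom on the direction that the trial expects.

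For correlation the difficulty is one of fit. Chi-square cannot be applied to two continuous quantities until they are cut into categories, and the article gives no cut-points. Taken literally, section 4.10 therefore does not yield a usable method for the analyses in section 4.4.

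At stake is avoidable loss of information in exploratory analyses of at most 56 patients.

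**Working it through.** **Sample size per arm (section 2.2).** The article's formula with its own inputs: [0.5×0.5 + 0.1×0.9] / (0.5 − 0.1)² × (1.96 + 1.282)² = 0.34 / 0.16 × 10.51 = 22.3, so 23. Allowing for loss, 23 × 1.2 = 27.6, so 28. Both stated figures reproduce. They belong to the main efficacy indicator; no power is stated for the grades or the correlations. They are used here only as the smaller and larger number of patients per arm.

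**Assumptions.** The article gives no grade distribution and no effect size for the grades. Six control distributions were assumed, with a common odds ratio that shifts every cut-point towards better grades. Example: control 50/30/15/5% from ineffective to recovery, odds ratio 3.
- Better than ineffective: odds 0.50/0.50 = 1, times 3 = 3, probability 0.75.
- Top two grades: odds 0.20/0.80 = 0.25, times 3 = 0.75, probability 0.43.
- Top grade: odds 0.05/0.95 = 0.053, times 3 = 0.158, probability 0.14.
- Treated arm: 25/32/29/14%.

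**Simulated power for the grades.** Two-sided 0.05, 20,000 runs per setting, 28 per arm; each cell shows 2×4 chi-square v tie-corrected rank-sum, in %.

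| Control, worst to best (%) | OR 2 | OR 3 | OR 4 | OR 6 |
|---|---|---|---|---|
| 90/7/2/1 | 6.2 v 14.1 | 15.9 v 31.1 | 29.5 v 50.2 | 56.2 v 77.5 |
| 70/20/8/2 | 15.0 v 24.7 | 36.1 v 54.5 | 57.2 v 75.1 | 82.6 v 93.6 |
| 50/30/15/5 | 17.0 v 28.0 | 42.0 v 59.8 | 62.7 v 79.5 | 86.0 v 94.8 |
| 40/35/20/5 | 17.9 v 28.5 | 42.0 v 60.0 | 61.7 v 79.0 | 85.4 v 94.7 |
| 30/40/20/10 | 18.3 v 28.9 | 42.0 v 59.9 | 63.6 v 80.8 | 85.9 v 94.9 |
| 25/25/25/25 | 19.1 v 29.2 | 42.8 v 60.5 | 62.5 v 79.2 | 84.1 v 93.9 |

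The gaps are about 8 to 11 points at OR 2, 15 to 18 at OR 3, 17 to 21 at OR 4 and 9 to 21 at OR 6. With 23 per arm the pattern is the same; for control 40/35/20/5% the figures are 34.2 v 51.4 at OR 3 and 52.3 v 71.2 at OR 4. Over both sizes the outermost gaps at OR 2 to 6 were 7 and 23 points. At OR 9 the gap can fall to 3 points, because both tests are then close to full power.

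**Analytic check.** Give both tests the same noncentrality and compare 1 with 3 degrees of freedom. Rank power of 80% needs about (1.96 + 0.842)² = 7.85; with 3 degrees of freedom that yields 64%. In the same way 50, 70 and 90% become 35, 53 and 78%. The loss is 12 to 17 points, in line with the simulation.

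**Effects that are not a consistent shift.** With 90/5/3/2% against 50/40/8/2%, both tests have 90% power. With 40/20/20/20% against 20/50/25/5%, chi-square has 68% and rank-sum 6%, because patients leave both extremes for the middle grades.

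**Correlation.** The passages can be set side by side. Section 4.4 plans correlations of abundances and metabolite levels with clinical endpoints and names no method. Section 4.10 names one method, for categorical data. No text says how the continuous values would be categorised, so no power loss can be attributed to the plan here.

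**The case against.** The strongest reply is that no sentence assigns the grades to chi-square. The listed endpoint is the TCM points score, recorded at screening and at weeks 3, 6, 9 and 12, and the efficacy index is a percentage. On those scales section 4.10 calls for the t-test or rank-sum test, which use order. This stands: the grades reach chi-square only by implication and only if they are tabulated. But the plan defines them, they are qualitative, and the text offers no other route.

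Second, the word for correlation may mean association between qualitative variables, with the microbe and metabolite analyses governed by the workflow and scripts of section 4.4. That reading is fair, and an article may leave the coefficient to a fuller document. What remains is that the one method printed for correlation does not fit the correlations described, so the wording needs clearing up.

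Three stronger readings are tempting and are not supported:
- *A general loss of 15 to 30 points.* For the grades the gap falls below 15 at small and at very large effects, and no run reached 30. Gaps near 30 arise only if continuous values are split at the median before correlating (with 56 patients and a true correlation of 0.4, Spearman 83% v chi-square 54%), and the article plans no such split.
- *Sparse cells make the P value unreliable.* A grade with fewer than 10 of 56 patients does have expected counts below 5 in both arms. Yet with no effect and 28 per arm, chi-square rejected in 3.3 to 4.7% of runs for five of the six distributions and in 2.0% for the most concentrated one. It errs on the cautious side; false positives are not inflated.
- *The trial's mechanistic claim rests on the grades.* The hypothesis in section 4.4 concerns microbiota, metabolites and immune microenvironment and does not mention them.

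**Conclusion.** The point holds as a minor mismatch between test and data. Under the rule in section 4.10, tabulated efficacy grades would be compared by a test that ignores their order, and the only named correlation method does not suit continuous measures.

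For the grades the cost is roughly 8 to 20 points of power at odds ratios 2 to 6 with 23 to 28 per arm. This rests on assumed grade distributions and on a shift that acts alike at every cut-point; the loss disappears or reverses when the effect is not monotone. For the correlations no size can be given from the article.

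The numeric TCM score is unaffected, the endpoints are exploratory with no claimed power, and neither the 6-month PFS rate nor the log-rank comparison of PFS is touched.

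**What to change.** Reword section 4.10 along these lines: ordered outcomes (the TCM efficacy grade, and ECOG if tabulated) are compared with the Wilcoxon rank-sum test or a proportional-odds model, the latter reported as an odds ratio with 95% confidence interval; correlations among continuous measures use Spearman coefficients; chi-square is kept for binary and unordered counts, with Fisher's exact test where expected counts are small. Check that the pre-defined scripts of section 4.4 say the same.

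The cost is a sentence or two of text. These methods are available in SPSS 26.0, and no new data or patients are needed.
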